### Blinding

Due to the nature of the intervention, participants and physical therapists cannot be blinded to group allocation. However, participants will be blinded to the expected outcomes, unaware of the study hypotheses, and will be explicitly instructed not to discuss their training program with the assessors to maintain assessor blinding. A trained assessor who is blinded to group allocation will be responsible for all outcome assessments. Data analysts and statisticians will also be blinded to group allocation.

### Intervention

The balance telerehabilitation intervention is based on the theoretical framework described in the ABC program for PD that we have previously published [28, 33, 40, 41]. Participants will be randomized at a 1:1 ratio into receiving home-based balance exercises in either balance telerehabilitation, called Tele-ABC (experimental group), or unsupervised exercises, called unsupervised-ABC (control group). Both groups (Tele-ABC and unsupervised-ABC) will receive identical exercises (Table 1) with 3 levels of progressions (Table 2) which the physical therapist will tailor to each person. Each participant will be instructed to exercise three times per week for 60 min for approximately 4 weeks. The exercise program consists of 6 exercise ‘stations’ (Fig. 2) with 3 levels of difficulty per task. Each exercise will be challenged with speed/amplitude increases, sensory challenges (eyes closed or soft surface), and/or cognitive (dual-task training) additions. For the unsupervised-ABC group, the first session will be conducted in person with the physcial therapist, which is common in clinical care – an in-person session to instruct in exercise followed by the person doing the exercises unsupervised at home. This is particularly true when people live in rural locations without easy access to physical therapy. Level of perceived exertion (0–10 scale) will be recorded for each station weekly by the physical therapist (experimental group—Tele-ABC) and in a paper journal (control group – unsupervised-ABC) [42]. The level of self-reported exertion will be recorded to determine the level of challenge of the program.

**Table 1 Tab1:** Physiological constraints in Parkinson’s disease that affect balance and exercise

Constraint	Impact on balance and mobility	Exercise principles	Exercise examples
*Rigidity*	Flexed posture ↓Trunk rotation ↓Range of motion	↑Axial rotation ↑Reciprocal movements ↑Upright posture ↑Limits of stability ↑Big steps	Kayaking Shoulder roll
*Bradykinesia*	Small and slow movements ↓Base of support	↑Size of APA ↑Base of support	Clock lunges Speed skater
*Impaired Sensory Integration*	↓Kinesthetic awareness Overutilization of vision Instability on unstable surfaces	↓Use of visual and proprioceptive input ↑Kinesthetic awareness	Cone tap standing on foam and wearing sunglasses
*Reduced Executive Function and Attention*	↓ Performance with dual tasks ↓Ability for complex sequencing of actions	↑Performance with dual task (cognitive or motor)	Boxing with cognitive dual task Tai Chi
*Freezing*	↓APA ↓Visuospatial skills ↓Mobility with divided attention	↑Weight shifting ↓Use of visual and auditory cues Layer exercises with dual task	Footwork drills: progressing to wearing sunglasses and adding dual task
*Inflexible Program Selection: task planning and sequencing*	↓Performance on functional transfers: sit-to-stand, rolling, floor transfers ↓Ability to quickly change strategy	↑Performance of sequencing components of transfers ↑Ability to quickly change strategies	Floor exercises including rolling and getting on/off the floor

*Abbreviations*: *APA* Anticipatory postural adjustment

**Table 2 Tab2:** Levels and progression of each exercise station

Exercise station	Level	Safety modifications	Sensory level	Speed level (metronome)	Dual-task level
**Tai Chi (10 min)**: prayer wheel, cat walk, cloud hands	1	UEs on counter/chair	None	None	None
	2	Hands hovering or near the wall	None	None	None
	3	No UE support	None	None	None
**Kayaking (5 min)**: basic stroke	1	Seated	Eyes open	Slow: 25 bpm	None
	2	Standing leaning against the counter	Eyes closed	Medium: 35 bpm	Easy level (cognitive^a^, motor^c^)
	3	Standing without support	Foam pad	Fast: 45 bpm	Hard level (cognitive^b^, motor^d^)
**Agility (15 min):** footwork drill, speed skater, toe taps	1	UE support on chair or counter	None	None	None
	2	No UE support	Sunglasses	None	Easy level (cognitive^a^, motor^e^)
	3	No UE support + movement	Foam pad	None	Hard level (cognitive^b^, motor^f^)
**Boxing (5 min)**: jab/cross/upper cut combo	1	Standing leaning against counter	Eyes open	metronome can be used	None
	2	Standing without support	Eyes closed	metronome can be used	Easy level (cognitive^a^)
	3	Standing without support + stepping	Foam pad	metronome can be used	Hard level (cognitive^b^)
**Lunges (5 min)**: clock stepping	1	UE support on chair or counter	Eyes open	metronome can be used	None
	2	No UE support	Sunglasses	metronome can be used	Easy level (cognitive^a^, motor^g^)
	3	No UE support + head rotation R/L with each step	Foam pad	metronome can be used	Hard level (cognitive^b^, motor^h^)
**Strength and Flexibility (15 min)**: sit to stand, bridge, shoulder release, cobra, trunk extension, cat camel	1	Bed	None	None	None
	2	Floor transfer with UE	None	None	None
	3	Floor transfer without UE support	None	None	None

*Abbreviations*: *UE* Upper extremities, *R* Right, *L* Left

^a^cognitive task: verbal fluency (e.g., naming animals, countries, fruits, girl/boy name) and serial subtraction (3 or 7 starting at 100)

^b^cognitive task: serial subtraction (3 or 7 starting at 5000), counting backwards, spelling backwards, saying alphabet backward, naming a girl/boy name for every letter of the alphabet, repeating back each name each time (e.g., A Annabel, A Annabel B Becky, A Annabel B Becky C Catthy, etc.)

^c^motor task: march in place

^d^motor task: march in place with knee kick

^e^motor task: ball toss/catch

^f^motor task: balance ball on the cone with movement

^g^motor task: reach in the direction of the step

^h^motor task: ball catch

**Fig. 2 Fig2:**
[figure not shown]
Exercise stations used in the exercise programs

### Safety issues

All adverse events, either during physical therapy or during data collection in the home and/or virtually will be recorded and reported. Falls and musculoskeletal strains are the greatest risks for exercise in patients with PD who have balance and gait impairments. An initial home visit by the physical therapist and customized levels of exercise progression and modification will help ensure safety in the home during exercise sessions.

### Assessment procedures

The pre-screening for inclusion/exclusion criteria will be done over the phone. All assessments will take place at the participant’s home and/or virtually. Immediately after the home and virtual assessments at baseline, participants will complete 7 days of daily-life mobility monitoring and then start the 12 intervention sessions (experimental or control). Following the 12 sessions, participants will complete post-testing repeating the home and virtual assessments and daily-life monitoring for 7 days. An overview of the study assessments is detailed in Table 3. All the participants will be assessed at the same time of day and in the clinically defined ‘‘on’’ state (fully medicated).

**Table 3 Tab3:** Overview of the study assessments and intervention period

Outcome Assessments	Pre-exercise: Home Visit	Pre-exercise: Virtual Visit	Pre-exercise: 7 days of Sensors During Daily Life	12 sessions of exercise intervention	Post-exercise: Home Visit	Post-exercise: Virtual Visit	Post-exercise: 7 days of Sensors During Daily Life
Mini-BESTest *(primary outcome)*	X				X		
Instrumented L-shape mobility test with wearable sensors		X				X	
ISAW with wearable sensors	X				X		
Daily-life mobility with instrumented socks and wearable sensor			X				X
MDS-UPDRS	X				X		
ABC	X				X		
PDQ-39	X				X		
NFoGQ	X				X		
FES-I	X				X		
IPAQ	X				X		
5 times sit-to-stand task	X	X			X	X	
360-degree Turn Test (right and left)	X	X			X	X	
Floor Transfer Test	X				X		
Self-Efficacy for Exercise	X				X		
Life-Space Questionnaire	X				X		
TSS					X		
HEP					X		
TabCAT	X				X		
Timed-up-and-go test		X				X	
Self-perceived Mini-BESTest		X					
PGIC					X		

*Abbreviations*: *Mini-BESTest* Mini Balance Evaluation Systems Test, *ISAW* Instrumented Stand and Walk Test, *MDS*-*UPDRS* Movement Disorder Society-Sponsored Revision of the Unified Parkinson’s Disease Rating Scale, *ABC* Activities-Specific Balance Confidence, *PDQ-39* Parkinson’s Disease Questionaire-39, *NfoGQ* New Freezing of Gait Questionnaire, *FES-I* Falls Efficacy Scale-International, *IPAQ* International Physical Activity Questionnaire- Short Form, *TSS* Telerehabilitation Satisfaction Scale, *HEP* Home Exercise Program, *PGIC* Patient Global Impression of Change, *TabCAT* Tablet-based Cognitive Assessment Tool

### Home-based, in-person pre- and post-exercise

In the home, the following assessments will be performed: i) the Mini-BESTest, a 14-item test of balance shown to be related to fall risk in people with PD [43]; ii) ISAW with and without a cognitive task (serial subtraction by threes from a three-digit number) where participants will wear 6 Opal sensors (APDM Wearable Technologies, a Clario company) placed over feet, lumbar area, wrists, and sternum. Participants will be instructed to look straight ahead for 30 s, walk straight ahead for 7 m, turn 180 degrees, and return to the initial starting location; iii) The MDS-UPDRS I-IV to assess PD-related non-motor experiences of living, motor experiences of daily living, motor severity, and motor complications [44]; iv) the Activities-Specific Balance Confidence (ABC) scale to assess the participant’s perception of balance confidence [45]; v) the Parkinson's Disease Questionaire-39 (PDQ-39) to assess how PD affects the quality of life over the last month [46]; vi) the New Freezing of Gait Questionnaire (NFoGQ) to assess the severity of FOG [47]; vii) the Falls Efficacy Scale-International scale to assess fear of falling [48]; viii) the International Physical Activity Questionnaire-Short Form (IPAQ) to assess the intensity and type of physical activity performed in the last 7 days [49]; ix) the five times sit-to-stand task [50]; x) the 360 degrees Turn test [51]; xi) the floor transfer test [52]; xii) the Self-efficacy for exercise scale to assess the participation in exercise [53]; xiii) the Life-Space Questionnaire to assess mobility based on how far and how often a person travels inside and outside home space [54]; xiv) cognitive function assessment using the Tablet-based Cognitive Assessment Tool (TabCAT) tests on an iPAD to assess visuospatial and executive function (Benton Judgement of Line Orientation, Flanker test, and Set Shifting test) [55–57]. At the post-test assessment, participants will complete all assessments performed at the pre-test and also the Telerehabilitation Satisfaction Scale (TSS) to assess the overall satisfaction with the telerehabilitation program [15] and the Patient Global Impression of Change (PGIC) to assess the impression of change after intervention [58].

### Home-based virtual pre- and post-exercise

Virtually (using home computer, iPAD, or study computer) we will administer: i) an instrumented L-shape mobility test where participants will wear 3 sensors (one Opal sensor on a belt with the sensor placed over the lumbar area and two Opal instrumented socks by APDM Wearable Technologies, a Clario company, placed on both feet) and will be instructed to sit for 30 s, then stand with feet together and look straight ahead for 60 s, walk at least 10 steps before turning 90 degrees, and take at least 5 steps to complete an L-shaped path, turn 180 degrees, walk back and finish an L-shaped path. The participants will perform 5 repetitions of an L-shape path continuously, and end with 30 s of quiet sitting. This instrumented L-shape mobility test can characterize multiple domains of balance (*see details of balance outcome in *Table 4), similar to the Mini-BESTest, including postural sway in standing with feet together with eyes open for 30 s before step initiation and gait with a 180-degree turn [11]; ii) the five times sit-to-stand task [50]; iii) the 360 degrees Turn test [51]; and iv) the 3 m timed-up-and-go test [59]. Self-perceived Mini-BESTest, where the participant is asked to image how well they would perform on the balance tasks of the Mini-BESTest will be assessed only in the pre-exercise assessment.

**Table 4 Tab4:** Objective balance and gait outcome measures collected at home with both virtual instrumented L-shape mobility test and daily-life mobility monitoring (7 days), divided by balance domains

*Balance and Gait Domains/Measures*	*Virtual instrumented L-shape mobility test, 3 wearable sensors*	*Daily-life mobility with passive monitoring, 3 wearable sensors*
Postural Sway		
Root Mean Square, Mediolateral	X	No
Root Mean Square, AnteroPosterior	X	No
Jerk, Mediolateral	X	No
Anticipatory Postural Adjustment (APAs)		
Peak Mediolateral	X	No
First Step Range of Motion	X	No
Gait: average		
Gait speed	X	X
Angle at Heel Strike	X	X
Stride length	X	X
Turning: Average		
Duration	X	X
Velocity	X	X
Angle	X	X
# Steps	X	X
Gait Variability		
Gait Speed	No	X
Angle at Heel Strike	No	X
Stride length	No	X
Swing Time	No	X
Duration	No	X
Velocity	No	X
Angle	No	X
# Steps	No	X

### Daily-life monitoring pre- and post-exercise

Participants will wear Opal Instrumented Socks that are made of a thin elastic cloth and have inertial sensors embedded for the measurement of mobility in daily life. When worn, the sensors are located on the dorsum of the foot with the battery above the lateral malleolus, as previously published [38]. They will also wear an Opal sensor on a belt with the sensor placed over the lumbar area (Opal and Opal instrumented socks by APDM Wearable Technologies, a Clario company). Participants will don the sensors in the morning and wear them for at least 8–10 h per day for 7 days. The sensors will be taken off and placed in a charger each night. At the end of the 7 days, the sensors will be returned by mail or picked up from their home by a study team member. See details of balance and gait outcomes in Table 4.

### Primary and secondary outcome measures

The Mini-BESTest will be the primary outcome, while objective balance and gait measures, daily-life mobility, instrumented executive function tests, and clinical scales described in Tables 4 and 5 will be secondary outcomes.

**Table 5 Tab5:** Clinical and functional outcomes measures

*Name*	*Description*
Mini-BESTest	14-item assessment of 4 balance domains: anticipatory, reactive, sensory, and dynamic gait
ISAW with wearable sensors	Quiet stance for 30 s, walk 7 m, turn 180 degrees, and return to the initial location in single and dual tasks (normal speed)
MDS-UPDRS	Clinical scale of severity of non-motor experiences of daily living, motor experiences of daily living, motor examination, and motor complications
ABC	16-item self-report scale of confidence in performing daily activities
PDQ-39	39-item self-report questionnaire to assess Parkinson’s disease-specific health-related quality in eight domains of quality of life
NFoGQ	9-item self-report scale of freezing of gait severity
FES-I	16-item questionnaire to assess fear of falling
IPAQ	Short Form to assess the intensity and type of physical activity performed in the last 7 days
5 times sit-to-stand task	Time to complete 5 repetitions sit-to-stand as quickly as possible
360 Degree Turn Test (right and left)	Time to complete fast 360 degrees to turn left and right as quickly as possible
Floor Transfer Test	Time to transfer from standing to laying down on back on the floor as quickly as possible
Self-Efficacy for Exercise	9-item self-report scale of efficacy for exercise
Life-Space Questionnaire	5-item self-report scale of life-space level
TSS	15-item self-report scale of satisfaction with the telerehabilitation program
HEP	15-item self-report scale of satisfaction with the home-based exercise program
TabCAT	Instrumented executive function using an IPAD
Timed-up-and-go test	Rise from a chair, walk 3 m, turn 180 degrees, return to the chair, and sit down (normal speed)
Self-perceived Mini-BESTest	14-item self-perceived assessment of 4 balance domains: anticipatory, reactive, sensory, and dynamic gait
PGIC	Patient rating the impression of change after intervention

*Abbreviations*: *Mini-BESTest* Mini Balance Evaluation Systems Test, *ISAW* Instrumented Stand and Walk Test, *MDS*-*UPDRS* Movement Disorder Society-Sponsored Revision of the Unified Parkinson’s Disease Rating Scale, *ABC* Activities-Specific Balance Confidence, *PDQ-39* Parkinson’s Disease Questionaire-39, *NfoGQ* New Freezing of Gait Questionnaire, *FES-I* Falls Efficacy Scale-International, *IPAQ* International Physical Activity Questionnaire- Short Form, *TSS* Telerehabilitation Satisfaction Scale, *HEP* Home Exercise Program, *PGIC* Patient Global Impression of Change, *TabCAT* Tablet-based Cognitive Assessment Tool

### Data management and monitoring

Data entry will be handled by the team members. Data will be entered into REDCap and the OHSU Balance Disorders database. Hard copies of these records will be stored inside a locked office in a locked cabinet at OHSU. The de-identified Mobility Lab data will be collected on a password-protected and data-encrypted laptop computer and uploaded after each test session to an OHSU secure server, where the Balance Disorders database is located. The computer that will store the project database will be protected by current network security behind the OHSU firewall. All data will be double-checked for accuracy by a person who is not involved in the day-to-day life of the study.

### Sample size calculation

#### Aim 1

To estimate power and sample size for relating the instrumented L-shape mobility test collected virtually in the home to the Mini-BESTest in-person, we used the pilot data from 114 people with PD who had measures on the Mini-BESTest and the ISAW – both performed in-person in the Balance Disorders Laboratory. Using multiple linear regression, we used a subset of objective measures to predict the Mini-BESTest total score as well as the four Mini-BESTest domain sub-scores. The subset of objective measures was selected based on bivariate correlations between the objective measures and the Mini-BESTest total score. A correlation at or above 0.4 was retained and included: 1) gait speed, 2) angle of the foot at heel strike, 3) stride length, 4) turning duration, 5) turning velocity, 6) steps during turning, and 7) range of motion of the 1^st^ step. These objective measures accounted for 48% of the explained variance in the Mini-BESTest total score and between 26–40% in the four Mini-BESTest subscores. We used this range of R^2^ as the parameter in our power calculations. Power was estimated at alpha equal to 0.05 and a sample size of 80. We will have at least 97% power to detect R^2^ of 0.26 or greater.

#### Aim II

One of the goals of Aim II is to generate preliminary estimates of the sensitivity of balance measures (Mini-BESTest and ISAW) due to the Tele-ABC program. These estimates ultimately will be used to inform power and sample size computations for a larger clinical trial. We did examine effect sizes detectable by intervention at the planned sample size and related these to effect sizes observed in other similar interventions. In our pilot study, we observed improved dual-task gait speed using the same, wearable mobility sensors after an in-person balance exercise intervention [41]. We observed an effect size of 0.94 (95%CI 0.67, 1.21). Using the means and standard deviations from these data (0.79 m/s and 0.92 m/s (pre and post means); 0.20 (sd)), we estimated the power to detect a change in dual-task gait speed with our proposed sample size of 40 participants (experimental group) using a paired sample t-test. With alpha set to 0.05, we will have approximately 96% power to detect changes in gait speed in the experimental group. Although the intervention proposed here is relatively small and not designed to be a highly powered trial itself, we will make use of a randomized, two-group intervention design.

#### Aim III

One of the goals of Aim III is to generate preliminary estimates of effect size for daily life metrics measured in the home after rehabilitation, for both the groups (experimental and control). These estimates ultimately will be used to inform power and sample size computations for a larger clinical trial. Specifically, we will calculate effect size estimates from 5 main home metrics that are predicted to be the most likely to show improvement after rehabilitation (turn angle, swing variability [coefficient of variation], the angle at heel strike, the angle at heel strike variability [coefficient of variation], and stride length variability [coefficient of variation]). Using paired sample t-tests, we estimate that we will have at least 80% power to detect pre/post differences with moderate effect sizes (Cohen’s d = 0.45) or greater with 40 participants at an alpha level of 0.05.

### Statistical analysis

#### Aim I

To determine if a virtual, balance assessment (instrumented L-shape mobility test) using wearable sensors can predict a gold-standard, clinical in-person assessment of balance (Mini-BESTest), we will use multiple linear regression. We will fit linear regression models with the total Mini-BESTest score, in addition to the four Mini-BESTest domain sub-scores. To determine the optimal set of predictors, we will employ three separate analytic approached to select predictors: 1) assess predictors based on their individual contribution to total R^2^ while considering their statistical significance; 2) stepwise selection method in linear regression models; and 3) advanced statistical learning approaches such as best subset regression analysis, LASSO regression, and random forest classifiers. Subsequent models will be adjusted for relevant covariates. Adjustments will be performed for multicomparison purposes.

#### Aim II

The primary outcome, Mini-BESTest score, and its subscores, pre and post-exercise will be compared between the two groups. Secondary outcomes described in Tables 4 and 5 will also be examined. We will use three statistical procedures: 1) linear mixed models will be used having a group (experimental and control) and time (pre and post-exercise) as fixed factors with included interaction (group x time) to indicate a difference of changes in outcomes between the groups. Individual random effects will also be included. Adjustments will be used for multicomparison purposes. Analyses will first be conducted without including other covariates, but followed by models with covariates (e.g., age, gender, body mass index, disease severity, freezing of gait, and cognition) to account for potential confounding effects; 2) analysis of covariance on delta change controlling for baseline measures. Covariates will be included in the subsequent analysis; and 3) the pre-post change in outcomes after each intervention will be compared between groups via independent t-tests (no covariates) and effect size with confidence interval. The estimates from this pilot study will be used to inform the sample size for a future clinical trial.

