### Recruitment, randomization, and allocation

Subjects will be recruited from the OHSU Movement Disorders Clinic, the OHSU Parkinson Center of Oregon and Movement Disorders clinical program, the Balance Disorders Laboratory, the Oregon Clinical & Translational Research Institute, local neurologists (at Portland Metro area hospitals and clinics), community recruitment (e.g., public talks and distribute study flyers at various community outreach events and locations, such as the Senior Living Centers, Athletic Clubs, Rotary Clubs, Parkinson Support groups).

This trial will enroll 80 eligible people with PD who will be randomized at a 1:1 ratio into the experimental group (*n* = 40) or control group (*n* = 40). Both groups will perform 12 sessions of exercise at home, with each session lasting 60 min, over approximately 4 weeks. Within 24 h after baseline testing the participant will be randomized using an online module in the Research Electronic Data Capture system (REDCap). The participant will learn their random group assignment after both enrollment and the baseline testing. The randomization module in REDCap allows the randomization of participants based on the Hoehn & Yahr stage. The module also monitors the overall allocation progress and assignment of randomized subjects. We used a stratified randomized block design to allocate participants to the either experimental or control group. Randomization to arms is balanced 1:1 for each stratum, Hoehn & Yahr I and II, and Hoehn & Yahr III, respectively. We additionally used randomly permutated blocks of 2, 4, and 6 in order to keep the randomization scheme blinded to the blinded research team members to help avoid selection bias. All subjects will agree not to change their exercise activities or antiparkinsonian medication during the duration of the study, unless necessary.

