#### Aim III

To determine if daily-life mobility changes after interventions, our main analysis will be the paired t-tests to compare the values in each metric described in Table 4 in the pre and post-exercises, separately. We will use the same statistical procedures as described in Aim II to explore improvement (estimated) between groups since no study has investigated the effects of any intervention on daily-life mobility using instrumented socks with wearable sensors.

Missing data: We will first assess the missing data frequency and patterns for both primary outcomes. If ≤ 5% of observations are missing the primary outcome, then multiple imputation methods will not be of benefit and we will perform analysis without imputation. If > 5% of observations are missing outcomes, we will perform multiple imputations as necessary to address the missing-ness. For all analyses, level of significance will be set at *p* ≤ 0.05.

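### The primary Mini-BESTest comparison has three unranked analyses; one should be named as primary, preferably the baseline-adjusted ANCOVA with the Hoehn & Yahr stratum added

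*Protocol article*

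**What the plan says.** In the protocol article, Statistical analysis, Aim II, the comparison is introduced as "The primary outcome, Mini-BESTest score, and its subscores, pre and post-exercise will be compared between the two groups". Three procedures follow, numbered but not ranked; the list opens with "We will use three statistical procedures: 1) linear mixed models will be used having a group".

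1. A mixed model with group, time and individual random effects, "with included interaction (group x time) to indicate a difference of changes in outcomes between the groups". On covariates: "Analyses will first be conducted without including other covariates, but followed by models with covariates". The list is given as examples: "e.g., age, gender, body mass index, disease severity, freezing of gait, and cognition) to account for potential confounding effects".
2. An "analysis of covariance on delta change controlling for baseline measures", with covariates added in a later run.
3. An independent t-test on the pre-post change, without covariates, plus an effect size with confidence interval.

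A sentence inside procedure 1 promises adjustment for multiple comparisons but gives no method and no family of tests. The end of the Aim III section sets p ≤ 0.05 for every analysis.

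The randomisation section says: "Randomization to arms is balanced 1:1 for each stratum, Hoehn & Yahr I and II, and Hoehn & Yahr III, respectively". That two-level factor is not named in any analysis.

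The missing-data paragraph begins "We will first assess the missing data frequency and patterns for both primary outcomes". The abstract, Table 3 and the section on primary and secondary outcome measures each name one primary outcome, the Mini-BESTest.

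**The concern.** Several p-values will answer the same treatment question, and nothing says which of them decides or what happens if they disagree. The result can then be read from whichever is favourable, so the stated 0.05 is not the real error rate.

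The procedures also differ in precision. The article says its estimates will inform the sample size of a later trial. A change-score analysis and a baseline-adjusted analysis give different effect estimates and different residual variances, so leaving the choice open also leaves that planning input open.

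A smaller matter is the target of the primary test. The subscores stand in the same sentence as the total score, and the missing-data rule speaks of two primary outcomes, so it is unclear what triggers the 5% imputation rule.

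**Working it through.** **Inputs.** From the article: 80 participants, 1:1, so 40 per arm; two visits; significance level 0.05 (two-sided assumed, since sidedness is not stated). Assumed: pre-post correlation rho of the Mini-BESTest within arm, 0.3 to 0.9; equal SD at both visits.

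**The plan's own figure.** The only Aim II power statement is about 96% for dual-task gait speed within the experimental arm. With d = (0.92 − 0.79)/0.20 = 0.65 and n = 40, the paired t-test has non-centrality 0.65 × √40 = 4.11 and power 98.0%. If 0.20 is the raw SD and the correlation is 0.4, d = 0.65/√(2 × 0.6) = 0.593 and power is 95.5%. The figure is broadly reproduced, but it concerns another outcome and no between-group contrast, so it does not help to rank the three procedures. No power is stated for the between-group Mini-BESTest comparison.

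**Step 1: how many distinct tests.** With two visits, complete data and a random intercept, the group by time coefficient is the difference in mean change, and its standard error is that of the t-test on change. On one simulated data set the mixed model gave 0.06507 (SE 0.16729, t = 0.38898) and the t-test gave 0.06507 (t = 0.38898). Adding a two-level baseline factor to the mixed model as a main effect left the interaction at 0.06507 with SE 0.16729. Procedures 1 and 3 are therefore one test, and main-effect covariates in procedure 1 do not alter it.

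**Step 2: precision.** With unit variance at each visit:
- change score: variance 2(1 − rho)
- ANCOVA: residual variance 1 − rho²
- ratio: (1 − rho²)/[2(1 − rho)] = (1 + rho)/2

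**Step 3: chance that either test is positive under the null.** The change equals (post − rho × pre) − (1 − rho) × pre, and the first term is uncorrelated with pre. The correlation between the two test statistics is therefore √[(1 + rho)/2]. The bivariate normal probability that at least one exceeds 1.96 in absolute value follows. It was also simulated (8,000 runs, 40 per arm, allocation balanced within stratum; 30% of patients in stage III and a stratum effect of 0.8 SD, both assumed). Monte Carlo standard error is about √(0.07 × 0.93/8000) = 0.3 points.

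| rho | Correlation of tests | Either positive, normal theory | Either positive, simulated | Also ANCOVA with six covariates, simulated | Variance ratio | Participants for the precision of 80 |
|---|---|---|---|---|---|---|
| 0.3 | 0.81 | 7.8% | 7.1% | 8.0% | 0.65 | 52 |
| 0.5 | 0.87 | 7.3% | 6.8% | 7.7% | 0.75 | 60 |
| 0.7 | 0.92 | 6.8% | 6.6% | 7.7% | 0.85 | 68 |
| 0.8 | 0.95 | 6.5% | 6.5% | 7.2% | 0.90 | 72 |
| 0.9 | 0.97 | 6.0% | 6.0% | 7.0% | 0.95 | 76 |

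A second simulation (5,000 runs per rho) gave 7.6% falling to 6.5% for either test at rho 0.5–0.8, and 8.8% falling to 7.3% with a covariate-adjusted ANCOVA added. The formula for independent tests (1 − 0.95² = 9.8% for two, 1 − 0.95³ = 14.3% for three) overstates the problem because the tests are highly correlated.

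**Step 4: each test alone.** In the 8,000-run simulation the rejection rate was 5.0–5.3% for the change score, 4.0–5.4% for ANCOVA without the stratum and 4.5–5.5% with it. No single test is inflated.

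**Step 5: what the stratum adds.** Simulated power for an assumed effect of 0.5 SD:

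| rho | Change score | ANCOVA | ANCOVA with stratum |
|---|---|---|---|
| 0.5 | 60% | 70% | 72% |
| 0.7 | 82% | 87% | 87% |
| 0.8 | 93% | 95% | 96% |

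Almost all of the gain comes from the baseline score.

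**The case against.** The trial is a pilot. Aim II sets out to explore effects and produce preliminary estimates, and the article says the trial is not meant to be highly powered. An excess of one to three points in the error rate does little harm to that purpose, and it arises only if results announced together are reported selectively. The more precise ANCOVA is already planned, and a fuller analysis plan may rank the procedures. All of this is fair and lowers the severity. It does not remove the point: the article states a superiority hypothesis, a primary outcome and a significance threshold, and it commits to three analyses of equal standing. In Aim III, by contrast, it does name a main analysis.

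The multiplicity sentence might be thought to settle the matter. It names neither method nor family and sits within procedure 1, so it does not.

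Some stronger readings are not supported.

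- A reader might infer that leaving out baseline or stratum inflates false positives. Step 4 shows that it does not; the excess comes only from the choice between procedures.
- A reader might infer that the mixed model decides because it is listed first, so that the precision is lost. The article gives it no such status.
- A reader might infer that omitting the stratum makes the standard errors seriously wrong. In the simulation the effect was small and, at low rho, conservative (4.0%). Disease severity, one of the example covariates, could mean Hoehn & Yahr stage, although the article does not say so.
- A reader might infer that the covariate-adjusted mixed model is bound to adjust nothing. That holds only for main effects and complete data; the article does not say how covariates enter, and it allows for missing outcomes.

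The reference to two primary outcomes is probably a slip, since the next sentence uses the singular.

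**Conclusion.** The point holds as one that should be fixed. The primary comparison rests on two distinct unadjusted tests, plus covariate-adjusted versions, with no ranking. Choosing between the two after seeing results gives a false-positive chance of about 6–8% instead of 5%, for rho between 0.3 and 0.9. The ANCOVA has 0.75–0.90 of the change-score variance at rho 0.5–0.8 (0.65–0.95 over the wider range), so it is the natural choice. Naming the stratum follows the design and adds from a fraction of a point to about two points of power under the assumed stratum effect. These sizes depend on an unstated correlation, equal SDs and complete data; the equivalence of procedures 1 and 3 depends on complete data.

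**What to change.** In the Aim II analysis section, name one primary analysis: ANCOVA of the Mini-BESTest total (post score or change, which give the same arm effect once baseline is in the model) on arm, baseline Mini-BESTest and Hoehn & Yahr stratum (I–II versus III), reporting the arm effect with its 95% confidence interval at two-sided 0.05.

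Label the mixed model and the t-test as sensitivity or descriptive analyses; the t-test can stay as the source of the unadjusted effect size. Where the mixed model takes covariates, enter each with a time interaction. Treat the subscores as secondary. In the missing-data paragraph, refer to the single primary outcome.

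The cost is wording, plus two degrees of freedom relative to the unadjusted t-test (78 to 76 with 80 complete participants). The change should be made before allocation is revealed to the analysts.
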